**2. Design**

1. **Sample:**

Emory Healthcare chaplain residents will be asked to view the empathic accuracy video scenarios and complete questionnaires at four time points during the residency year. Chaplains will be asked to wear ambulatory recording devices that record chaplain-patient interactions.

Emory Healthcare patients will be asked to complete self-report assessments before and after their Spiritual Health consult. Patients will be informed of chaplains use of ambulatory recording device for research purposes.

No children, prisoners or other vulnerable populations will be included in this study.

*Inclusion Criteria*: Chaplain residents with Spiritual Health at Emory Healthcare or patient of Emory Healthcare.

*Exclusion Criteria*: None

b. **Setting:**

Consenting chaplains will view the empathic accuracy videos and complete the study questionnaires at one or more of the Emory Healthcare campuses (EUH, EUHM, Saint Joseph’s, Emory Johns Creek, and Wesley Woods).

Consenting patients will complete self-report assesments and spiritual health consults at one or more of the Emory Healthcare campuses (EUH, EUHM, Saint Joseph’s, Emory Johns Creek, and Wesley Woods).

c. **Recruitment:**

Chaplain residents and Emory Healthcare patients will be approached in person at the Emory Healthcare campuses by a researcher and will provide written consent.

d. **Procedures**:

Participants will be approached by a researcher who will explain the study to them and have them sign an informed consent document if they understand the study component and are interested in participating. Chaplain resident participants will receive the CBCT as part of their clinical pastoral education (CPE) curriculum. Chaplain resident participants will receive the CBCT either in the first educational unit (the early-start group) or approximately midway through the residency year (the delayed-start group). Residents in the early-start group will meet virtually for a didactic approximately every two weeks to discuss their residency experience in the context of their CBCT knowledge and caregiving approach. Residents in the delayed-start group will meet for a similarly structured and scheduled didactic on spiritual health topic(s) unrelated to patient care. After the delayed-start group receives CBCT approximately midway through the residency year, the students in the delayed-start group will also meet virtually for the CBCT-focused didactic to discuss their residency experience in the CBCT context and the early-start students will receive the spiritual health didactics on topic(s) unrelated to patient care. All didactics will be 1.5 hours in length. All chaplain resident participants will view the empathic accuracy video and complete the questionnaires at four times during the residency year: before the early-start group receives CBCT (baseline, or T0); after the early-start group completes CBCT (T1); before the delayed-start group receives CBCT (T2), and after the delayed-start group completes CBCT (T3). A subset of the chaplain residents will be interviewed at three time points relative to their training in CBCT. The interviews consist of open-ended questions to further query their learning experiences with CBCT. Researchers will compare differences in the mean scores of empathic accuracy and resiliency measures over time.

[figure not shown]

During their training program, chaplain residents will provide spiritual consults to patients throughout the Emory hospital system. We will examine whether patient (n = 300) outcomes are improved for those receiving chaplain spiritual care augmented by CBCT, in comparison to those receiving spiritual care from chaplains who receive CBCT at the end of their residency program. To this end, study personnel will shadow chaplain residents in both groups and will administer self-report assessments of negative symptomology (depression, anxiety, and loneliness) and well-being (quality of life, hope) to consented patients. In addition, study personnel will audio record chaplain-patient interactions. Patient outcomes will be gathered from retrospective chart reviews and will include use of opioid pain medication, duration of stay, patient’s denial of care, and patients’ Press Ganey satisfaction scores.

In a final step, using patient chart reviews we will examine chaplain and patient factors that may mediate the link between spiritual consults and improved patient outcomes. Specifically, we will examine whether chaplain empathic accuracy or self-reported compassion mediate the impact of spiritual care consults on patient health outcomes. We will also examine whether patients’ well-being (hope, quality of life), or negative symptoms (depression, anxiety, loneliness) mediate the impact of spiritual care consults on patient health outcomes.

We will also use the ambulatory ambulatory audio recordings of the chaplain-patient interactions to interrogate which aspects of the chaplain-patient interaction mediate improved patient outcomes (see Figure 4). Spiritual consult audio recordings will be coded by 2 trained, independent CBCT instructors for CBCT content. They will also be coded for linguistic and behavioral elements derived from existing models of compassionate interaction in the hospital environment[^9^](#_ENREF_9).

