**Specific Aim 4: To evaluate whether CBCT-informed interventions improve patient outcomes.**

Upon completion of their training program, chaplain residents will provide spiritual consults to patients throughout the Emory hospital system. We will conduct comprehensive assessments in order to examine whether patient (n = 300) outcomes are improved for those receiving chaplain spiritual care augmented by CBCT, in comparison to those receiving spiritual care from chaplains who receive CBCT later in their residency. To this end, study personnel will shadow chaplain residents in both groups and will administer self-report assessments of negative symptomology (depression, anxiety, and loneliness) and well-being (quality of life, hope) to consented patients. In addition, study personnel will audio record chaplain-patient interactions. Patient outcomes will be gathered from retrospective chart reviews and will include use of opioid pain medication, duration of stay, patient’s denial of care, and patients’ Press Ganey satisfaction scores.

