- (15 min) **Empathic Accuracy (EA) Task**[**^8^**](#_ENREF_8)**:** a dynamic video assessment that asks subjects to continuously rate the emotions of others as they tell emotional autobiographical stories.
- (2 min) **Spiritual Meaning Scale (SMS)**[^20^](#_ENREF_20): a 15-item, likert-scale inventory that assesses the extent to which someone endorses a belief in something larger than themselves.
- (4 min) **Jefferson Scale of Empathy**[^21^](#_ENREF_21)^,^[^22^](#_ENREF_22): a 20-item scale designed to measure empathy in practicing health care professionals and health care professional students. It has been translated into 53 languages and has been used in more than 80 countries.

Total time required for completion of measures is approximately 45 minutes. All measures will be delivered digitally.

- 1. **Post Patient Consult Checklists**
- (2-4 min) **Post-Visit Checklist for CBCT:** a 41-item checklist that assesses the encounter the CBCT-trained Chaplain Resident had with the patient; including how/if the Resident prepared for the consult, assessed the patient’s state of mind, used specific tools and skills during the consult, and how well the Resident thought the encounter went.
- (2 min) **Post-Visit Checklist for non-CBCT:** a 17-item checklist that assesses the encounter the non-CBCT-trained Chaplain Resident had with the patient; including how/if the Resident prepared for the consult, assessed the patient’s state of mind, used specific tools and skills during the consult, and how well the Resident thought the encounter went.

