**Patients**

- (<1 min) **NCNN Distress Thermometer**[**^23^**](#_ENREF_23)**:** a single-item distress thermometer that compares favorably with longer measures used to screen for distress.
- (1 min) **PROMIS Self-Efficacy for Managing Emotions**[**^24^**](#_ENREF_24)**:** a likert-27-item scale that measures a subject’s level of confidence to manage and control symptoms of anxiety, depression, helplessness, discouragement, frustration, disappointment, and anger.
- (2 min) **PROMIS Positive Affect**[**^25^**](#_ENREF_25)**:** a 15-item likert-scale that asseses momentary positive or rewarding affective experiences such as feelings and mood associated with pleasure, joy, elation, contentment, pride, affection, happiness, engagement and excitement.
- (4 min) **Hospital Anxiety and Depression Scale (HADS)**[**^26^**](#_ENREF_26)**:** a 14-item questionnaire that is widely used for detecting anxiety and depressive disorders.
- (2 min) **PROMIS Emotional Support**[**^27^**](#_ENREF_27)**:** a 4-item likert-scale that assessed perceived feelings of being cared for and valued as a person.
- (2 min) **PROMIS Informational Support**[**^28^**](#_ENREF_28)**:** a 4-item likert-scale that assesses perceived availability of helpful information or advice.
- (2 min) **PROMIS Social Isolation**[**^29^**](#_ENREF_29)**:** a 4-item likert-scale that assesses perceptions of being avoided, excluded, detached, disconnected from, or unknown by, others.
- (4 min) **Scottish Patient Reported Outcome Measure (PROM)**[**^30^**](#_ENREF_30)**:** an 18-item likert-scale that assesses how a hospitalized patient felt about the Pastoral Care visit both during the consult and after it. It also assesses the patients present state regarding their situation and whether they see themselves as a spiritual or religious person.

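### In Aim 4, study personnel both shadow the chaplain and administer the patient self-reports, with no masking, separation of roles or private completion stated, so the post-consult self-reports are open to expectancy bias

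*Protocol*

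**What the plan says.** Specific Aim 4 compares patients seen by CBCT-augmented chaplains "in comparison to those receiving spiritual care from chaplains who receive CBCT later in their residency". On data collection it states that "study personnel will shadow chaplain residents in both groups and will administer self-report assessments". The Procedures part of the Design section repeats this ("study personnel will shadow chaplain residents in both groups and will administer self-report assessments of negative symptomology (depression, anxiety, and loneliness) and well-being") and adds: "In addition, study personnel will audio record chaplain-patient interactions". The Training section assigns data collection to one named individual or that person's research assistants.

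Under Sample, "Emory Healthcare patients will be asked to complete self-report assessments before and after their Spiritual Health consult". The patient measures cover distress, affect, anxiety and depression, support and isolation. They also include the Scottish PROM, which "assesses how a hospitalized patient felt about the Pastoral Care visit both during the consult and after it".

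Residents fill in a post-visit checklist that differs by group. CBCT-trained residents have "a 41-item checklist that assesses the encounter the CBCT-trained Chaplain Resident had with the patient"; the others have a 17-item form.

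The protocol has two provisions that come near this issue. The Audio Recordings section withholds identities from those who code the recordings. The statement that all measures are delivered digitally closes the list of chaplain questionnaires. Neither covers the collection of patient self-reports. The Data analysis section compares the patient self-reports between groups with independent-samples t-tests.

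**The concern.** The post-consult outcomes are subjective and are given to study staff who may have just watched the consult. If those staff have recognised CBCT content, they know the group before the patient answers. Expectancy could then affect how a form is introduced, how an unclear item is explained, or how much help is given. A shift of this kind that differs between groups enters the mean difference directly, and a two-group t-test cannot tell it from an effect of the CBCT-informed consult.

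Two features add to the exposure. The Scottish PROM items about the visit can have no pre-consult value to set against them. And the patient self-reports are candidate mediators in Aim 5, so a biased group difference there would carry into the mediation models. The Synopsis says that the pilot data will be used to estimate efficacy and inform a randomised trial, so a distorted estimate would also carry into that trial's planning.

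**Working it through.** **Which safeguards exist?** The relevant provisions are:

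| Question | What the protocol provides |
|---|---|
| Who shadows the chaplain? | Study personnel, in both groups (Aim 4; Procedures) |
| Who administers patient self-reports? | Study personnel, same sentence (Aim 4; Procedures) |
| Are these staff masked to group? | Not stated |
| Are the two tasks kept apart? | Not stated |
| Do patients answer unobserved? | Not stated; patients complete the forms (Sample; Setting) |
| Any masking elsewhere? | Only for coders of recordings (Audio Recordings) |
| Digital delivery? | Stated for the chaplain measures only |

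**Which outcomes are exposed?**
- Post-consult self-reports, including the Scottish PROM: yes, if staff learn the group during the consult.
- Pre-consult self-reports: only if staff already know the group, because these precede the consult content.
- Opioid use, duration of stay, denial of care and Press Ganey scores: no, because they come from retrospective chart review.
- Chaplain outcomes of Aims 1 to 3: not collected by this route.

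**How much could a shift matter?** The protocol states the number of patients ("We will examine whether patient (n = 300) outcomes are improved") but gives no split, alpha, SD or detectable difference for Aim 4, so there is no figure to reproduce. Everything below except the total of 300 is an assumption: 150 per group, two-sided 5% test, independent observations, no true effect, and a differential shift of b SD on the scale analysed.

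The standard error in SD units is sqrt(1/150 + 1/150) = 0.1155. The test statistic is centred at b/0.1155, and the rejection probability is Φ(b/0.1155 − 1.96) + Φ(−b/0.1155 − 1.96).

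- b = 0.1: centre 0.866, rejection about 14%
- b = 0.2: centre 1.732, rejection about 41%
- b = 0.3: centre 2.598, rejection about 74%

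With a 100:200 split the standard error is sqrt(1/100 + 1/200) = 0.1225, and shifts of 0.1, 0.2 and 0.3 SD give about 13%, 37% and 69%.

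For scale, the difference detectable with 80% power at 150 per group is (1.960 + 0.842) × 0.1155 = 0.32 SD. A shift of 0.2 to 0.3 SD is therefore of the same order as an effect this comparison could detect.

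**Clustering by chaplain.** The figures above ignore it. Take 300/30 = 10 patients per chaplain and an assumed ICC of 0.05. The design effect is 1 + 9 × 0.05 = 1.45, so the statistic of the planned unadjusted t-test has SD sqrt(1.45) = 1.204. Rejection at b = 0.2 is then Φ((1.732 − 1.96)/1.204) = about 43%, and at b = 0.3 it is Φ((2.598 − 1.96)/1.204) = about 70%. These include the inflation that ignoring clustering causes by itself: with b = 0 the rate is 2 × Φ(−1.96/1.204), about 10%.

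**The case against.** Several points limit the concern.

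- **One individual in both roles.** A reader might infer that the person who shadows a chaplain always collects that patient's forms. The text names study personnel collectively. One person doing both is the natural reading, and the small team in the Training section makes it likely, but it is not stated.
- **Knowledge of group.** A reader might conclude that staff will know the group. This too is inferred. Learning it from the consult is plausible, but the checklists are the resident's own account and nothing says that shadowing staff see them.
- **Self-completion.** The Sample and Setting sections have patients completing the assessments. Administering may mean no more than handing over a form, and the protocol describes no interviewing. What remains unstated is privacy and how help is given.
- **Every patient-reported outcome.** It is tempting to say that all of them are compromised. Press Ganey satisfaction is patient-reported but comes through chart review, and pre-consult scores are mostly outside the route.
- **Courtesy towards the chaplain's companion.** Shadowing takes place in both groups and the protocol does not say that patients know the group. Reluctance to criticise the visit would therefore act in both and need not create a difference. Staff expectancy is the clearly differential route.
- **No analysis could help.** This is too strong. The chart outcomes are a comparison outside the route, and a record of who assisted would allow partial checks.
- **Status of the study.** It is a naturalistic pilot whose named primary outcomes are chaplain measures.

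These points narrow the scope and rule out any claim about actual size. They do not supply the missing safeguard. Who collects outcomes, and under what conditions, is study conduct that this protocol itself sets, and an SAP would not normally repair it afterwards.

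**Conclusion.** The concern holds in limited form. As written, the plan allows staff who attended the consult, and may have recognised the chaplain's group, to administer subjective post-consult forms, including the rating of that visit, with no masking, separation of roles or private completion stated. Differential bias in those self-reports is possible, and the planned t-tests would not remove it. Aim 4's staff-administered self-reports are affected, as is their use as mediators in Aim 5. The chart outcomes and the chaplain primary outcomes are not.

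The documents do not show that bias will occur, in which direction, or how large it would be. The 41% and 74% figures illustrate sensitivity under an assumed shift, an assumed equal split, independent observations and a two-sided 5% test. They do not estimate the trial's actual error rate.

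**What to change.** In Specific Aim 4 and in the Procedures part of the Design section, replace the wording that has study personnel administer the self-reports. State instead that patients complete the before and after forms themselves, digitally or on a form they seal, out of view of the chaplain and the shadowing staff member. Keep the residents' post-visit checklists away from anyone who handles patient forms. Where a patient needs help, limit it to reading items verbatim, record who gave it, and use existing staff who did not attend the consult where they are available.

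The cost is a short amendment. Digital delivery is already planned for the chaplain measures, though extending it to patients would have to be stated. Some inpatients will still need help, so the exposure is reduced and not removed. Requiring a second helper unaware of group for every such patient could need extra staff across five campuses and is not part of this recommendation.

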**Figure 3: Study schematic**

**Cognitively-Based Compassion Training (CBCT)**

The compassion meditation technique that will be incorporated into the spiritual caregiver training program has been adapted and secularized by the contemplative principal investigator for the project, [name]., senior instructor in the Department of Religion and spiritual director of Drepung Loseling Monastery, Inc., in Atlanta. Although secular in presentation, the compassion meditation program is derived from Tibetan Buddhist mind-training (Tibetan *lojong*) practices. These practices derive largely from writings ascribed to the Indian Buddhist teachers Shantideva (8^th^ Century) and Atisha (11^th^ Century) (The Dalai Lama, 2001) and differ in important ways from the mindfulness-based practices that have received most of the scientific attention in recent years. Whereas mindfulness-based practices emphasize the development and maintenance of a non-judgmental stance toward thought processes and emotional reactions,[^10^](#_ENREF_10) lojong practices utilize a cognitive, analytic approach to challenge one’s unexamined thoughts and emotions toward other people, with the long-term goal of developing altruistic emotions and behavior towards all people [^11^](#_ENREF_11).

Lojong-based compassion meditation has two primary elements: an initial phase in which various arguments are examined that challenge one’s common sense notion of other people as falling into the categories of “friend, enemy and stranger” and a second phase in which one practices developing spontaneous feelings of empathy and love for an ever expanding circle of people, beginning with an exploration of the interdependence of one’s own life with that of others and then cultivating a sense of gratitude, even for strangers and eventually for apparent adversaries. Within the Tibetan Buddhist tradition, concentrative (i.e. shamatha) and mindfulness (i.e. vipassana) practices are typically employed as valuable preliminary techniques for establishing the focus and awareness necessary to engage in specific compassion practices [^11^](#_ENREF_11). In keeping with this tradition, in the current study subjects are introduced to attentional and mindfulness-based techniques (modules 1 - 2) to help improve attention and awareness prior to commencing specific lojong compassion practices in training modules 3-6. The training protocol is highly iterative, such that by the end of presenting the 6 modules, each student’s daily meditation practice will begin with a brief period of *shamatha* and *vipassana* to calm and focus the mind, followed by analytical practices designed to challenge unexamined assumptions regarding feelings and actions toward others with a focus on generating spontaneous empathy and compassion for themselves and others.

CBCT includes didactic teaching combined with meditations aimed at cultivating the following skills, and proceeds according to the following outline:

1. Developing Attention and Stability of Mind: The foundation for the practice is the cultivation of a basic degree of refined attention and mental stability.
2. Cultivating Insight into the Nature of Mental Experience: The stabilized mind is then employed to gain insight into the nature of the inner world of thoughts, feelings, emotions and reactions.
3. Cultivating Self-Compassion: The student participant observes the innate aspirations for happiness and wellbeing as well as those for freedom from unhappiness and dissatisfactions, i.e., which mental states contribute to fulfillment and which ones prevent it. The participant then makes a determination to emerge from the toxic mental and emotional states that promote unhappiness.

1. Developing Equanimity: Normally one tends to hold fast to categories of friends, enemies, and strangers and to react unevenly to people, based on those categories, with over-attachment, indifference and dislike. By examining these categories closely, the participant comes to understand their superficiality and learns to relate to people from a deeper perspective: everyone is alike in wanting to be happy and to avoid unhappiness.
2. Developing Appreciation and Gratitude for Others: Although people view themselves as independent, self-sufficient actors, the truth is that no one can thrive or even survive without the support of countless others. When the participant realizes interdependence with others and the many benefits which others offer every day, the participant develops appreciation and gratitude for them.
3. Developing Affection and Empathy: Deeper contemplation and insight into the ways in which myriad benefits are derived from countless others, along with awareness that this kindness should by rights be repaid, enables the participant to relate to others with a deeper sense of connectedness and affection. By relating to others with a profound sense of affection and endearment, the participant is able to empathize deeply with them. The participant cannot then bear to see others suffer any misfortune and rejoices in their happiness.

1. Realizing Wishing and Aspirational Compassion: Enhanced empathy for others, coupled with intimate awareness of their suffering and its causes, naturally gives rise to compassion: the wish for others to be free from suffering and its conditions.

1. Realizing Active Compassion for Others: In the final step, the participant is guided through a meditation designed to move from simply wishing others to be free of unhappiness to actively committing to assistance in their pursuit of happiness and freedom from suffering.
2. **Measures:**

